## Discussion

This article describes the design of a study evaluating the effectiveness of an intervention on the occurrence of finger/wrist, ankle, shoulder and knee injuries among adult recreational volleyball players. This study will be one of the first randomized prospective controlled trials in recreational volleyball that looks at the occurrence of both acute and overuse injuries.

The two major challenges of this study are related to the recruitment of a large number participants and the monitoring of both exposure and injuries. A total of 456 volleyball players across 46 teams (10 players per team on average) and two competition regions are enrolled in the study. The selection of the two largest competition regions in The Netherlands was based on practical reasons. In these two regions, a total of 2797 adult teams across 507 clubs are available, which should be sufficient to reach and enroll 456 participants. Also, holding explanatory group meetings for coaches about the purpose and procedures of the study remains more efficient when those meetings are geographically located nearby the enrolled clubs. For the monitoring of volleyball exposure and injuries, coaches and players are asked to complete an electronic questionnaire every two weeks during the whole 2017–2018 season. Even if not time consuming for most participants (likely to remain uninjured), completing a questionnaire every two weeks remains a substantial task for all participants that might play a role in the recruitment and follow-up of participants as well. However, completing such an electronic questionnaire every two weeks is needed to monitor accurately the occurrence of especially overuse injuries. In sports injury epidemiology, recording overuse injuries has always been a problem as athletes are often likely to continue their sport participation despite their complaints. In our study, the use of the reliable and valid OSTRC questionnaire will allow us to record over time both acute and overuse injuries, adding an unequivocal and unique value to the existing sports injury epidemiological evidence.

After the systematic development of ‘VolleyVeilig’, a randomised prospective controlled trial enables to assess its effectiveness on the one-season occurrence of finger/wrist, shoulder, knee and ankle injuries among recreational adult volleyball players. The results of this trial will contribute to the successful nationwide implementation of ‘VolleyVeilig’ in all volleyball clubs in The Netherlands, and ultimately to the reduction of injury occurrence.

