### Sample size

Analogous to previous studies about the effect of preventive interventions in volleyball [7] and in other sports [8, 9], the assumption is that a 40% injury reduction will be achieved over one season in the intervention group by comparison to the control group. To achieve 80% power with a significance level of 0.05, an injury prevalence estimate of 0.25 in the control group and a loss to follow-up among players of 15% over one season (no multiple cluster randomization), the sample size calculation reveals that 640 volleyball players are needed in the study [4]. Consequently, we will strive to enroll 64 teams (average of 10 players per team) assigned either to the intervention or the control group (equal number of 32 teams in each group). The teams within the intervention and control groups will be matched according to their competition level.

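### The Sample size section requires 640 players (64 teams), the Discussion gives 456 (46 teams), and the article does not reconcile the two

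*Protocol article*

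**What the plan says.** The Sample size section of the protocol article sets out the calculation: "To achieve 80% power with a significance level of 0.05, an injury prevalence estimate of 0.25 in the control group", with 15% of players lost over the season. The effect is given as "the assumption is that a 40% injury reduction will be achieved over one season in the intervention group". The result is that "the sample size calculation reveals that 640 volleyball players are needed in the study", and the section continues "we will strive to enroll 64 teams (average of 10 players per team"), split equally into 32 teams per group. Clustering by team is not allowed for.

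The Discussion, where it turns to recruitment, states: "A total of 456 volleyball players across 46 teams (10 players per team on average) and two competition regions are enrolled in the study". Two sentences later it says that the two regions hold 2797 adult teams in 507 clubs, "which should be sufficient to reach and enroll 456 participants".

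No section explains a move from 640 to 456, changes an assumption or restates the power.

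**The concern.** One article gives two sizes for the same trial. Both use ten players per team, so team size does not account for the difference. The larger number carries the power claim. The smaller one is described as what is enrolled, and it is also the number for which the feasibility of recruitment is argued.

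At stake is whether the 80% power statement describes the trial that is run. If the true size is 456, the chance of missing the hypothesised 40% reduction is roughly 31% to 35% instead of 20%, and the article does not say so. If the true size is 640, the feasibility argument in the Discussion is made for the wrong number.

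**Working it through.** **Inputs** (Sample size section): control proportion p1 = 0.25; a 40% reduction gives p2 = 0.25 × 0.60 = 0.15; alpha 0.05; power 80%; equal groups; 15% loss. The article does not state whether the test is one- or two-sided. Two-sided is assumed here.

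**Step 1: reproduce 640.** Two-proportion formula with mean proportion 0.20:

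- Uncorrected n per arm = [1.960 × √(2 × 0.20 × 0.80) + 0.842 × √(0.25 × 0.75 + 0.15 × 0.85)]² / 0.10² = (1.109 + 0.472)² / 0.01 = 250.0.
- With continuity correction: n′ = (250.0 / 4) × [1 + √(1 + 4 / (250.0 × 0.10))]² = 62.5 × (1 + 1.077)² = 269.6 per arm.
- With 15% loss: 2 × 269.6 / 0.85 = 634. Rounding up within each arm gives 270, then 318, so 636 in total.
- 318 per arm rounds up to 32 teams of ten, hence 64 teams and 640 players.

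So 640 is a sound result of the stated inputs. Without the correction the total is 588 (590 with rounding per arm). The unpooled and arcsine versions give 584. None of these two-sided variants comes near 456.

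**Step 2: the gap.** 640 − 456 = 184 players; 64 − 46 = 18 teams; 456 / 640 = 71%.

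**Step 3: power for 25% against 15% at each size.** With n evaluable players per arm, power = Φ{[0.10 − c − 1.960 × √(0.32 / n)] / √(0.315 / n)}, where c = 0 without correction and c = 1/n with it. For 456 with 15% loss, n = 456 × 0.85 / 2 = 193.8:

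- uncorrected: (0.1000 − 0.0796) / 0.0403 = 0.505, power 69%;
- corrected: (0.1000 − 0.0052 − 0.0796) / 0.0403 = 0.377, power 65%.

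| Enrolled | Loss | Evaluable per arm | Power, corrected | Power, uncorrected |
|---|---|---|---|---|
| 640 | 15% | 272 | 80% | 83% |
| 456 | 15% | about 194 | 65% | 69% |
| 456 | none | 228 | 72% | 76% |

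Fisher's exact test gives 81%, 65% and 73% for the three rows, in line with the corrected column.

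**Step 4: reduction detectable with 80% power at 456 and 15% loss.** Solving the same expression for p2:

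- corrected: p2 = 0.133, a reduction of 1 − 0.133 / 0.25, or about 47%;
- uncorrected: p2 = 0.138, about 45%.

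The corrected value is the one that matches the formula behind 640.

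**Step 5: how far these figures reach.** They treat players as independent, as the Sample size section does. For illustration only, assume a within-team correlation of 0.01 to 0.05 and 8.5 evaluable players per team; neither value is in the article. The design effect is then 1 + 7.5 × 0.01 = 1.075 to 1 + 7.5 × 0.05 = 1.375, and power at 456 falls to about 61% to 50% corrected (66% to 56% uncorrected). The effect of allocating one region per arm cannot be quantified from the article.

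**The case against.** The strongest reply is that the status of 456 is open. The Discussion uses it first as enrolment already achieved and then as a number that the regions should be able to supply. It could be a recruitment result, or a target left over from another version. The anticipated flowchart (Fig. 1) is not visible in the text available, so it cannot settle the matter. A reader might infer that the trial is definitely running 29% smaller and that its 80% power is lost. The text does not establish that: if 456 is a leftover, 640 stands and no power is lost. This part of the objection holds. What remains is that two explicit figures conflict under either reading.

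Second, a recruitment shortfall does not make an a priori calculation wrong, and the section says only that the team will strive for 64 teams. That also holds, and it is why the planned calculation should stay. It does not remove the need to state the consequence of a shortfall, because the same section says that 640 are needed.

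Third, 65% to 69% is not this trial's power. It comes from a comparison of two proportions between individuals. The Statistical analysis section plans Cox regression for acute injury and a comparison of mean prevalence for overuse injury, and the Study design and allocation section randomises two regions, one to each arm. This stands too: the figures show the size of the shortfall on the plan's own assumptions and no more.

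Finally, a reader might guess that 456 comes from a one-sided calculation. No section contains one or states a one-sided test, so this would be speculation, and the point does not rest on it.

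**Conclusion.** The article is internally inconsistent on trial size, and as written it must be reconciled. The calculation of 640 is not in error: it reproduces to within 1% (634 to 636). The figure of 456 does not satisfy the same inputs, even with no loss to follow-up.

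If 456 is the actual size, power for the hypothesised 40% reduction is about 65% (69% without continuity correction) after the planned 15% loss, against the stated 80%. This rests on a two-sided 5% test, 25% against 15%, equal arms and independent players. Positive correlation within teams would lower it further.

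**What to change.** State in the Discussion whether 456 players in 46 teams is achieved enrolment or a target, and carry one consistent size through the Sample size section and the Discussion.

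- **If 456 is the actual size:** keep the calculation of 640 as the planned target. Beside it, report the shortfall of 184 players and 18 teams. Add that, on the same assumptions, power for a 40% reduction is about 65% with continuity correction (69% without), and that 80% power is reached only for a reduction of about 47% (45% without). Label these values as indicative, because they come from an individual-level two-proportion test and ignore clustering by team and the allocation of one region per arm.
- **If 640 remains the target:** correct both mentions of 456 in the Discussion and the accompanying 46 teams. Restate the feasibility sentence for 640.

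Either change is wording only and leaves design, conduct and analysis as they are. In the first case the stated power becomes less favourable.

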## Abbreviations

Nevobo: Dutch Volleyball Federation
NTR: Dutch Trial Registry (Nederlands Trial Register)
OSTRC: Oslo Sports Trauma Research Centre
ZonMW: Netherlands Organization for Health Research and Development
